#### **7.4.2.1 Disease-Modifying COVID-19 Sensitivity Analysis**

To ascertain the possible impact of COVID-19 on the results of the disease-modifying analysis, a sensitivity analysis will be performed. The repeated measure model defined in Equation 5 will be fitted to the MDS-UPDRS part III scores in the OFF state, with imputation of the total scores undertaken regardless of the number of missing items, and will include an indicator variable that identifies whether the visit was completed during COVID-19 lockdown. The estimated coefficient and associated 95% confidence interval of the COVID-19 indicator variable will be used to understand the effect of COVID-19 on the disease-modifying analysis.

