### 2.1.1 Primary Outcome Measures

The primary outcome is change in MDS-UPDRS part III motor subscale score in the OFF state over 24 months. MDS-UPDRS part III score consists of 33 items, where each item is scored between 0 (normal) and 4 (severe). The OFF state is defined as the absence of the participant's regular PD medication so that the severity of the underlying disease is evident; more details can be found in section 2.3.

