### 4.10.1 Missing Primary Outcome Data

Summary statistics of the number of missing items, and frequencies and percentages of participants with missing items of the MDS-UPDRS part III score will be reported.

Provided all missing items of MDS-UPDRS part III are missing at random, the total score for a given participant can be imputed if a maximum of seven of the 33 possible items are missing. Alternatively, if the same item is missing across all participants for one follow-up time-point, a maximum of three items can be missing to allow for valid imputation of the total score for each participant.

In PD STAT, one item of the MDS-UPDRS part III was erroneously omitted from case report forms at all time-points. Question 15 should consist of two items, a score for postural tremor for each of the left and right hands. However, only one item response could be recorded and the case report form did not specify, or request specification of, which hand. For a small proportion of participants, the assessor manually annotated the case report forms and included postural tremor scores for the left and right hand. In these instances, the scores for both left and right hands will be used as part of the calculation of the primary outcome. However, if a participant only has one postural tremor score, the second postural tremor score will be treated as missing data (not at random).

For a maximum of three missing items, imputation of the MDS-UPDRS part III total score will be undertaken according to the following equation

$$D = \frac{A \times B}{C}$$

*Equation 1*

where  $A$  is the sum of the items scored,  $B$  is the total number of items which should have been scored (for MDS-UPDRS part III  $B = 33$ ),  $C$  is the number of items actually scored and  $D$  is the imputed score (i.e. total MDS-UPDRS part III score).

For the purposes of pre-defined sensitivity analyses of the primary outcome (outlined in section 7.3), the requirement of no more than three missing items will be relaxed.

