#### 4.10.3 Missing Data as a Consequence of COVID-19

Although the majority of outcomes can be completed remotely, due to the nature of some of the tasks, a small number of items/measurements cannot be assessed during remote visits. For the MDS-UPDRS part III, question 3 (rigidity, consisting of 5 items) and question 12 (postural stability, consisting of 1 item) cannot be assessed remotely. This will affect calculation of the primary outcome, total MDS-UPDRS part III assessed in the OFF state, and corresponding secondary outcome assessed in the ON state.

In addition, the ACE-III cannot be completed remotely, whilst completion of 10MWT is dependent on the suitability of the participant's house or outside space and completion of the BTT is dependent on a stable internet connection and the availability of a tablet or computer. Finally, outcomes derived from the blood test at 24 months will be missing for participants in the COVID-19 population.

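### The lockdown-indicator coefficient in section 7.4.2.1 mixes a scoring shift with any COVID-19 effect and does not show whether the disease-modifying result changed

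*SAP*

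**What the plan says.** SAP section 4.10.3 states that "question 3 (rigidity, consisting of 5 items) and question 12 (postural stability, consisting of 1 item) cannot be assessed remotely". Section 4.10.1 adds that "one item of the MDS-UPDRS part III was erroneously omitted from case report forms at all time-points", namely the second postural-tremor score. A small proportion of participants have both hands annotated, and for them: "In these instances, the scores for both left and right hands will be used as part of the calculation of the primary outcome".

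Equation 1 (section 4.10.1) is D = A × B / C. A is the sum of the scored items, B = 33, and C is the number of items scored at that visit. Section 4.10.1 treats up to seven missing items as acceptable under missing at random. The limit falls to three when the same item is absent for everyone at a time point. For the section 7.3 sensitivity analyses, "the requirement of no more than three missing items will be relaxed".

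Section 7.4.2.1 belongs to section 7.4 and sets its own rule: Equation 5 is refitted "with imputation of the total scores undertaken regardless of the number of missing items", with an added lockdown indicator. It then says, of the impact on the section 7.4.2 model: "The estimated coefficient and associated 95% confidence interval of the COVID-19 indicator variable will be used to understand the effect of COVID-19". No section restricts the face-to-face visits to the items that can also be scored remotely.

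**The concern.** Equation 1 in effect fills each missing item with the participant's mean over the items that were scored. That is harmless if the missing items resemble the rest. At a remote visit the missing items are the same six every time, fixed by the mode of visit: five rigidity items and one postural-stability item. If these run higher or lower than a participant's other items, that participant's total moves between a face-to-face and a remote visit with no change in the disease. The lockdown indicator marks nearly the same visits, so its coefficient picks up the movement.

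There is a second, separate difficulty. Section 7.4.2 says interpretation centres on the group difference at 26 months. A main-effect indicator estimates an average displacement of lockdown visits in both arms together. It cannot show whether the group difference altered. A report that followed section 7.4.2.1 could present a clear COVID-19 coefficient produced largely by the scoring rule, and still leave unanswered whether COVID-19 affected the disease-modifying result.

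**Working it through.** The SAP gives no figure for this shift, so there is none to reproduce.

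**Inputs from the SAP.** Part III has 33 items scored 0 to 4 (section 2.1.1). Six cannot be assessed remotely (4.10.3). One further item is usually missing at every visit (4.10.1). Items scored are therefore:

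- face-to-face: 33 − 1 = 32, or 33 if both hands were annotated;
- remote: 33 − 1 − 6 = 26, or 27 if both hands were annotated.

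**Algebra.** Let m be the mean of the remotely assessable items and q the mean of the six others, with no true change between visits.

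- Remote score: 33 × 26m / 26 = 33m.
- Face-to-face score: 33 × (26m + 6q) / 32.
- Difference: 33 × (6/32) × (m − q) = 6.19 × (m − q).
- With both hands annotated: 33m − (27m + 6q) = 6.00 × (m − q).

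**Size.** m and q are not in the SAP, so the gap is an assumption. As a check, Equation 5 plus the indicator was simulated with a participant random effect only. The assumptions were 150 participants, 20% of 26-month visits remote, no true change, and 60 repetitions.

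| m − q (assumed) | Shift by algebra | Mean simulated indicator coefficient |
|---|---|---|
| +0.5 | +3.09 | 3.14 |
| 0 | 0 | −0.04 |
| −0.25 | −1.55 | −1.57 |
| −0.5 | −3.09 | −2.85 |
| −1.0 | −6.19 | −6.30 |

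The indicator takes up the scoring shift almost in full, in either direction.

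**One illustrative record (assumed scores).** Rigidity is 2 on each of five items, postural stability 1, one tremor item 1, and the other 25 items average 1.2. The 26 assessable items sum to 31 and the six others to 11. Face-to-face: 42 × 33/32 = 43.3. Remote: 31 × 33/26 = 39.3. The apparent change is −4.0 points with no real change.

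**Treatment coefficient.** With m − q = −0.5 and an assumed 30% versus 10% of 26-month visits remote by arm, the mean 26-month group difference was 0.08 with the indicator in the model and −0.58 without it. The true value was zero.

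**Common-item scoring.** If every visit is scored from the same 26 items, the shift is zero by algebra. The simulated indicator coefficient at m − q = −0.5 was then 0.17, which is within simulation noise.

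**The case against.** The strongest reply is that nothing of consequence is biased. Section 7.4.2 focuses on the 26-month group difference, and the indicator protects that coefficient by absorbing the average shift. The analysis is a sensitivity check on unpowered, exploratory work that is considered only if Simvastatin is not futile. The main disease-modifying fit keeps the section 4.10.1 limits, so remote visits have no valid score there. The with/without comparison is therefore nearly available already, apart from one face-to-face visit on 25 March 2020. It can also be said that section 7.4.2.1 speaks of an effect on the analysis rather than on motor severity, and that lost items are themselves a consequence of the pandemic.

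Most of this stands, and it limits the point to how one coefficient is read. It does not rescue that reading. The SAP names the coefficient as the yardstick, yet the coefficient neither separates its components nor speaks to the treatment estimate.

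A reader might go further in three ways that the SAP does not support.

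- **That the futility result is contaminated.** The primary analysis keeps the three-item rule. Section 7.3.2 excludes remote visits, and section 7.3.3 compares arms within each population, where a shared shift cancels on average. Only the CACE analysis could be touched, and only if it is triggered and remote visits are unbalanced between arms. Assume 60 per arm and a shift of 3.09 points. A split of 6 versus 2 remote visits gives 4/60 × 3.09 = 0.21 points, or 0.26 after dividing by an assumed 80% compliance. A split of 8 versus 0 gives 0.41, or 0.52.
- **That a gap of 0.48 wipes out the 3-point margin.** The arithmetic is right (3/6.19 = 0.48), but it sets a within-visit shift against a between-arm difference.
- **That the SAP plainly breaks its own item limits.** Remote loss affects a subset of participants, not all of them at a time point. Seven missing items equals the missing-at-random limit numerically, although items lost because of visit mode do not obviously meet that condition.

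**Conclusion.** The point holds as one of interpretation. Unless a participant's rigidity and postural-stability items average the same as the other items, the lockdown coefficient in section 7.4.2.1 contains a scoring shift of about 6.19 × (m − q), or 6.00 × (m − q) where both hands were annotated. Across assumed gaps of 0 to 1 item point in either direction this runs from 0 to about 6.2 points. The SAP does not allow the size or the sign to be derived. The coefficient combines item loss, remote mode and any pandemic effect, and does not show whether the disease-modifying result changed. The treatment coefficients are largely protected while the indicator stays in the model. The multiplier is exact algebra. The sizes rest on assumed item means, and the simulation results on assumed numbers and splits of remote visits.

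**What to change.** 1. Replace the last sentence of section 7.4.2.1. Judge COVID-19 impact by setting the 24- and 26-month group differences (δ24* and δ26*, with 95% confidence intervals) from fits with and without the lockdown visits side by side. The face-to-face visit of 25 March 2020 counts as a lockdown visit. Keep the indicator in the fit that includes lockdown visits as an adjustment term, and state that its coefficient is not read as a COVID-19 effect. Sections 7.3.3 and 8.2.1 already compare treatment estimates in this way.
2. Add a supporting sensitivity fit in which every participant's score at every visit uses only the remotely assessable items (all except questions 3 and 12), rescaled by Equation 1.
3. State in sections 4.10.1 and 7.3.1 that the CACE analysis keeps the three-item rule, so that it uses the same scores as the primary analysis.

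The cost is a few sentences of SAP text and one derived score from item data already held. The drawback is that the common-item score leaves out rigidity and postural stability. It is not the full part III total and is not directly comparable with the main estimate, so it should support the with/without comparison and not replace it.

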Hence  $\alpha$  and  $\beta$  were chosen to reflect the futility design-based hypotheses, with the one-sided  $\alpha$  set at 10% and  $\beta$  at 20% (i.e. 80% power).

Based on a recently reported study at the time of the design of this futility trial, the expected mean increase in MDS-UPDRS part III from baseline to 12 months in the placebo group is assumed to be 2.2 points, with corresponding standard deviation of 7.3 points. Assuming that this increase in MDS-UPDRS part III is linear over time, gives an expected mean increase from baseline to 24 months of 4.4 points in the placebo group (i.e.  $\mu_p = 4.4$ ). Therefore, if we assume the MCID is -3, this implies the mean of the Simvastatin group,  $\mu_s$ , is 1.4 points. Additionally, we assume a slightly inflated standard deviation over this period of 7.5 points.

The sample size calculation was based on a two-sample t-test with a 10% one-sided alpha. Following the previously listed assumptions, the number of participants needed to follow-up at 24 months (i.e. with primary outcome data) is 57 participants per group, to provide 80% power to reject the null hypothesis of non-futility and declare futility.

This sample size was inflated to allow for a proportion of participants allocated to the Simvastatin group to stop taking the trial medication during the initial 1-month low dose phase. Assuming that this proportion was 15%, the above sample size was inflated by  $(1-0.15)^{-2}$ , to give 79 participants per group. Secondly, the sample size was adjusted to allow for a (non-differential) loss to follow-up rate of 20%. Accordingly, the sample size was further inflated by a factor of  $(1-0.2)^{-1}$ , to give a sample size of 99 participants per group and a total recruitment target of 198 participants commencing the higher dose phase of the study.

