#### 7.4.2 Disease-Modifying Analysis

If there is evidence from the primary analysis that Simvastatin is not futile, consideration will be given to performing additional analysis of the primary outcome to investigate a potential disease-modifying effect. Descriptive statistics (e.g. means and 95% CI) and plots of MDS-UPDRS part III by visit month and allocated group will be presented. Participants will be included in the disease modifying analysis if: (i) they have fully complied with the treatment protocol (i.e. definition (i) from section 4.4.2) and (ii) they have provided valid MDS-UPDRS III scores at least two time points according to the imputation requirements outlined in section 4.10.1.

A mixed effects, repeated measures model will be fitted to the primary outcome measured at baseline, 12, 24 and 26 months, with participants included as a random effect. This repeated measures model will allow for missing data, whilst also allowing for analysis of the two-period design of the washout phase.

Adjustments will also be made for the stratification variables, modified Hoehn & Yahr score as a fixed effect and recruiting site as a random effect, as well as patient-related factors, which may have a strong influence on disease progression, i.e. disease duration, gender and age at baseline, to account for potential influence on the primary outcome.

The repeated measure model to investigate a disease modifying effect is defined as

$$y_{i,j,t} = \delta^{12*} x_{1,i,j} I_{t=12} + \delta^{24*} x_{1,i,j} I_{t=24} + \delta^{26*} x_{1,i,j} I_{t=26} + \delta_1 t + \theta x_{i,j} + Z_i + U_{i,j} + \varepsilon_{i,j,t}$$

Equation 5

where  $\delta^{k*}$  is the allocated group difference at the  $k$  visit month. The terms  $y_{i,j,t}$ ,  $x_1$ ,  $\delta_1$ ,  $x_{i,j}$ ,  $\theta$ ,  $Z_j$ ,  $U_{i,j}$ ,  $\varepsilon_{i,j,t}$ ,  $I_{t=k}$ ,  $i$  and  $j$  are the same as defined in Equation 4, but  $k = 12, 24, 26$ , which include the 26-month visit and excludes baseline.

The study is not powered to determine whether the treatment is disease modifying. Therefore, the results of this analysis should be treated with caution, and interpreted as exploratory only. However, interpretation will focus on  $\delta^{26*}$ , where an estimate below zero may be indicative of a effect that persists after discontinuation of treatment, suggesting the possibility that the effect of simvastatin is disease modifying rather than merely symptomatic.

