### **8.2.1 COVID-19 Sensitivity Analyses of Secondary Outcomes**

In line with the draft guidance on the implications of the COVID-19 outbreak on methodological aspects of ongoing clinical trials, additional sensitivity analyses of all secondary outcomes for which at least one participant provided valid 24-month data during COVID-19 lockdown will be undertaken. Specifically, the analyses of each of the secondary outcomes will be repeated excluding participants who provided 24-month outcome data during COVID-19 lockdown when social distancing measures were in place (i.e. the non-COVID-19 population). Comparison of the treatment effect estimates from these sensitivity analyses against the estimates obtained from the primary analyses of the secondary outcomes will facilitate informal evaluation of the effect of the pandemic on the secondary outcomes.

The number of capsules and percentage of capsules returned every month will also be presented according to whether 24-month outcome data was collected face-to-face or remotely.

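### The COVID-19 check on the disease-modifying result reads the average score shift at lockdown visits, not the change in the 26-month group difference

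*SAP*

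**What the plan says.** Section 7.4.2.1 gives its purpose as "To ascertain the possible impact of COVID-19 on the results of the disease-modifying analysis". It refits Equation 5 with part III totals prorated however many items are missing, and adds one visit-level indicator for lockdown. The read-out is then stated: "The estimated coefficient and associated 95% confidence interval of the COVID-19 indicator variable will be used to understand the effect of COVID-19". The section mentions no group-by-lockdown term and no comparison of the group difference between fits.

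Section 7.4.2 says where the result itself lies. Interpretation rests on the 26-month group coefficient of Equation 5 (the starred delta, δ26 here), of which it says that "an estimate below zero may be indicative of a effect that persists" after treatment stops.

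The other two COVID-19 analyses are read differently. Section 7.3.3 compares the allocated-group coefficients of two models informally. Section 8.2.1 relies on "Comparison of the treatment effect estimates from these sensitivity analyses against the estimates obtained from the primary analyses of the secondary outcomes".

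Two further rules matter. Section 4.10.3 says that six part III items (five for rigidity, one for postural stability) cannot be scored remotely. Section 4.10.1 allows a total to be imputed with at most three items missing. It lifts that limit only for the section 7.3 sensitivity analyses, and section 7.4.2.1 lifts it for its own refit. The main disease-modifying fit in section 7.4.2 keeps the limit.

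**The concern.** The question and the read-out do not match. An additive indicator shared by both arms has the null hypothesis that lockdown visits score the same on average as other visits. The section asks whether δ26 is affected, and these can come apart in both directions:

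- A shift common to both arms gives a clearly non-zero coefficient with almost no effect on δ26. Prorating without the six unassessable items is a ready mechanism.
- A shift that differs by arm is partly or wholly averaged out of the coefficient, and an additive term does not remove it from δ26.

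The coefficient is also silent on visits that the main fit loses because the totals are invalid. What is at stake is whether the report says correctly that the 26-month finding is, or is not, robust to lockdown.

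**Working it through.** **The plan's own figure.** The point depends on no stated number, but the sample size section supplies a scale for the simulations. Section 4.2 uses a "two-sample t-test with a 10% one-sided alpha", a margin ("if we assume the MCID is -3"), an SD ("we assume a slightly inflated standard deviation over this period of 7.5 points") and enough participants "to provide 80% power to reject the null hypothesis of non-futility and declare futility". Per group, n = 2(1.2816 + 0.8416)² × 7.5²/3² = 56.35, so 57. Then 57/0.85² = 78.9, so 79; 79/0.8 = 98.75, so 99; and 2 × 99 = 198. All of this reproduces.

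**How a common shift arises.** Let m be the mean score of the 27 items that can be scored remotely and r the mean of the six that cannot. The full total is 27m + 6r and the prorated total is 33m. The shift is therefore 6(m − r). A shift of 3 points needs m − r = 0.5 on the 0 to 4 item scale, 4 points needs 0.67, and 5 points needs 0.83. The same six items are lost in both arms.

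**What the coefficient and δ26 pick up.** Let lockdown shift scores by aP (placebo) and aS (simvastatin), with lockdown visits balanced by arm and making up a fraction f of 26-month visits. To first order:

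- indicator coefficient ≈ (aS + aP)/2;
- bias of δ26 in the fit with the indicator ≈ f(aS − aP).

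The first is the mean of the two shifts and the second depends on their difference. With aP = +4, aS = −4 and f = 0.2, these give 0 and −1.6.

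**Simulation of Equation 5.** Settings: linear time, group terms at 12, 24 and 26 months, random participant intercept, no true drug effect, 800 runs per setting. The SD of change is 7.5 (section 4.2), which is a residual SD of 7.5/√2 = 5.30. Assumed, because the SAP gives no figures: 120 or 160 participants, between-participant SD 10, and 10, 20 or 40% of 26-month visits in lockdown (5 to 15% at 24 months). Site and baseline covariates are left out. For 120 participants, with 20% in lockdown at 26 months and 5% at 24 months:

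| Lockdown shift | Mean coefficient | Its CI excludes 0 | δ26, indicator fit | Interaction CI excludes 0 | δ26, interaction fit |
|---|---|---|---|---|---|
| None | 0.08 | 4.4% | 0.06 | 5.9% | 0.06 |
| +4 both arms | 3.91 | 88% | 0.01 | 5.6% | 0.01 |
| +4 placebo, −4 simvastatin | 0.20 | 4.0% | −1.37 | 88% | 0.01 |
| −4 simvastatin only | −1.91 | 34% | −0.75 | 32% | −0.06 |

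The fitted bias of −1.37 is smaller than the first-order −1.6 because the mixed model also uses each participant's other visits.

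Ranges over all settings:

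- Common +4 or +5: the coefficient's CI excludes 0 in 70 to 100% of runs, with δ26 in the indicator fit within 0.1 of zero.
- Opposite shifts of 4: 4 to 7% of runs, with bias of 0.7 to 0.8, 1.4 and 2.9 points at 10, 20 and 40% lockdown.
- Simvastatin only: 24 to 61% of runs, with bias in the indicator fit of −0.3 to −1.5.

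**Which fit carries the bias.** A further run applied the section 4.10.1 limit and dropped lockdown scores from the main fit. It assumed 120 participants, 24 lockdown visits at 26 months and 8 at 24 months, SDs 9 and 5, +3 placebo and −3 simvastatin, 400 runs. Mean δ26 was −0.11 in the main fit (Monte Carlo error about 0.06) and −1.18 in the indicator fit. The group-by-lockdown model gave −0.11, matching the main fit. The interaction had a standard error of about 2.35, so its 95% CI spans about ±1.96 × 2.35 = ±4.6 points.

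**The case against.** The strongest reply is that a reader might infer more harm than the plan allows: that the check would look clean while lockdown scores pull the main δ26 below zero. The SAP does not support that. The main fit takes only totals valid under section 4.10.1. Remote visits miss six items, usually seven with the omitted second tremor score, so they largely stay out. The only face-to-face visit after 23 March 2020 that the SAP reports is the one on 25 March. An arm-specific shift would therefore bias the sensitivity fit, not the result it is meant to check. This stands.

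Three further points also stand:

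- The SAP sets no significance rule or action for the coefficient. The exclusion rates above describe how the interval behaves and are not false-alarm rates of a planned test.
- Complete masking needs shifts that nearly cancel between blinded arms, and no mechanism for that is apparent. With a shift in simvastatin only, the coefficient shows about half of it, and the interaction detects it about as often as the coefficient does (32% against 34% in the table).
- A fit that excludes lockdown visits would largely duplicate the planned main fit.

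None of this rescues the read-out. If the main fit is affected mostly by visits it loses, the coefficient is still the wrong quantity, because it describes only the scores put back in. The sensitivity fit does estimate δ26, but section 7.4.2.1 does not say to report or compare it.

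**Conclusion.** The point holds as a mismatch between aim and read-out. The coefficient named in section 7.4.2.1 measures the average shift in scores at lockdown visits and does not answer whether COVID-19 changed δ26. The likelier failure is a measurement shift from prorating being reported as an effect on the disease-modifying result. False reassurance is possible but needs shifts that differ by arm, and it is complete only when they nearly cancel.

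The direction follows from the form of the model. The sizes rest on assumed visit counts, SDs and shifts. The consequence is limited: section 7.4.2 only considers the analysis if simvastatin is not found futile, and calls it unpowered and exploratory. The primary futility test does not use this coefficient. The wording should still be corrected, because sections 7.3.3 and 8.2.1 already work from the right quantity.

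**What to change.** Replace the last sentence of section 7.4.2.1 with wording to this effect:

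- Report the 26-month and 24-month group differences with 95% CIs side by side from the planned main fit (Equation 5 under the section 4.10.1 limit) and the planned sensitivity fit (limit relaxed, lockdown indicator added). Give the number of visits by arm that each fit uses.
- Judge the impact of COVID-19 informally by the change in δ26 between the two fits, in line with sections 7.3.3 and 8.2.1.
- Add the group-by-lockdown interaction estimate with its 95% CI, labelled exploratory.
- Keep the indicator's main effect only as a description of measurement shift.

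The cost is one sentence of SAP text and one extra model fit on data already held. The interaction will be imprecise if lockdown visits are few (standard errors of 1.7 to 3.3 points in the simulated settings), so it should be read as an estimate with its interval and not as a test.
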